### Eligibility criteria

Phase 1: People aged between 18-60 years will be selected in a stratified manner (age and gender) and will be included in the study. For phase 2, (both experimental & control groups) block leaders and representatives from each colony who can read & write Kannada and are willing to participate will be included in the study. The exclusion criteria for both Phase 1 & 2 will be those individuals who have attended previous mental health workshops and those who have any acute/chronic illness.

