## Abstract

**Aim:** This study aims to build the capacity of the people at grass root level as gatekeepers of mental health. It will assess the effectiveness of the Gatekeeper Training Program (GTP) on gatekeeper behaviour, awareness, attitude, and mental help seeking intention.

**Design:** An evaluative research approach in two phases. Phase 1: Cross-sectional house-to-house exploratory survey. Phase 2: A quasi-experimental design with multiple follow ups at 0, 6 and 12 months.

**Method:** Data will be collected using standardized tools like Mental Health Knowledge Questionnaire (MHKQ), Community Attitude towards Mentally Ill (CAMIS), Mental Help Seeking Intention (MHSIS) and Gatekeeper Behavior Scale (GBS). For Phase 1, a house-to-house survey will be conducted among the selected colonies of Koraga tribe to determine their awareness, attitude, and mental help seeking intention regarding common mental health problems. Phase 2 includes identification of the leaders/representatives of the selected tribal colonies, and involving them in GTP. Pre-test and multiple post-test will be conducted in Phase 2 at 0, 6, 12 months.  The study is funded by Indian Council of Medical Research from 16 August 2021 for 3 years duration.

**Discussion:** Treatment gap in psychiatric disorders remains an issue of great concern. Evidence based research promotes task shifting approaches in dealing with mental health problems in the community. Capacity building programs like GTP for the underprivileged section of the society are important especially in low and middle income group of countries.

**Impact:** This need based GTP, will ensure mental health first aid in the society. Early identification of people with mental health problems at their doorsteps has huge impact on the prognosis of the illness, closing the treatment gap and stigma reduction.

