## Background

In the Toto tribe of the Sub-Himalayan region, the prevalence rate of mental illness was 48.97%, with depression being the highest (
Ghosh *et al.*, 2004). A recent study from the West Godavari district of Andhra Pradesh, predominantly comprising people from scheduled tribes, highlighted that 15% of the present generation of the tribal population was affected by common mental disorders like stress, depression, suicide risk, and anxiety (
Maulik *et al.*, 2017). According to National Health and Family Survey (NHFS) 3, 72% of tribal men aged 15-54 years were addicted to tobacco, and 50% of tribal men were addicted to alcohol (
Ministry of Health and Family Welfare & Ministry of Tribal Affairs, 2013). Psychosocial problems were also reported among high school children of the Mysuru region. About 23.7% of children in the tribal area had anxiety disorders, 1.6% had mood disorders, 3.2% had suicidality, and 2.2% were diagnosed with ADHD (
Pradeep *et al.*, 2018). Koraga, a particularly vulnerable tribal group of Udupi district has shown significant liver dysfunction due to chronic alcoholism among its population, irrespective of its gender. Most of the daily wages were spent on alcohol as evident by majority (75%) of them being alcoholics (
Mungli *et al.*, 2013). Several studies have found that in general there is a vast treatment gap when it comes to the accessibility of mental health services. Although there are several reasons for the same, lack of awareness and stigma towards mental illness and mentally ill people are the most prominent. A cross-sectional survey assessing the effectiveness of community mental health programs in a tribal area of South India revealed that the mean score on awareness regarding mental illness was 5.13±2.27 among its study population (
Yalsangi, 2011). However, contrary to this, the majority (64%) of people from Naga tribe could recognize the presence of a mental health problem in a depicted vignette (
Longkumer & Borooah, 2013). Another study on stigma in mental illness revealed that 38.5% of persons with severe mental illness (PSMI) were found poor, and this poverty was strongly associated with stigma related to mental illness (OR 2.60, 95% CI 1.27 to 5.31), and scheduled tribes (2.39, 1.39 to 4.08). Therefore, it was concluded that females or people from lower castes having severe mental illness were more at risk to be economically poor due to stigma related to mental illness (
Trani *et al.*, 2015).

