The Systematic Medical Appraisal, Referral and Treatment (SMART) mental health project of Andhra Pradesh found that 7% of people go to faith healers and religious leaders at the very beginning of their mental illness for treatment (
Maulik *et al.*, 2017). The preference for magico-religious healing and traditional practices to overcome mental health concerns is prevalent in South-Asian countries, evidenced by a qualitative study from Bangladesh on tribal communities (
Rahman *et al.*, 2012). As mentioned earlier, the study poses a challenge to the healthcare delivery system in low-income countries, which mainly caters to the plainland population. A randomized controlled trial across 32 colleges of USA evaluated the effectiveness of the gatekeepers training program and found that trainees' self-perceived knowledge, ability, and confidence to identify students in distress were increased (
Lipson *et al.*, 2014). In the long-term effects of community gatekeeper training, 15 (n=40) participants had helped someone at risk of suicide; also, intentions to help and confidence to identify someone at risk of suicide remained high (
Deane *et al.*, 2006). Though common mental health problems are prevalent among the tribal population, as evident by the research studies mentioned above, very little is done to improve their condition in India. Hence, it is vital to improve the mental health care system for our most primitive and underprivileged tribal people and develop effective mental health care programs at the grassroots level.

**Aims and Objectives:** The objectives of the study are to:
•Determine the awareness, attitude and mental help seeking intention regarding common mental health problems among the tribal population using standardized tools.•Assess the awareness, attitude, mental-help seeking intention and gatekeeper behavior among the leaders/representatives of Koraga tribe regarding common mental health problems using standardized tools.•Find out the effectiveness of gatekeeper training program on awareness, attitude, mental help seeking intention and gatekeeper behavior among the leaders/representatives of Koraga tribe regarding common mental health problems.•Determine the number of vulnerable individuals identified, counselled, referred to a tertiary center as and when needed by the trained gatekeepers of the tribal community at 12 months of follow up.

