### Sample size

Phase 1 sample size is calculated using the formula as mentioned below. In this formula the confidence level is 95%, hence Z
^2^ = 1.96. Here proportion of the tribal people having awareness regarding common mental health problems was assumed to be 0.5 and (d) is the precision of the study (corresponding to the effect size) = 0.05.

$$n=\frac{Z^{2}P\;\left(1-P\right)}{d^{2}}=384\approx 400$$

For Phase 2: Using G* power software the sample size was estimated to be 86 (43 in each group).

With 20% attrition rate n = 108 (54 in each group).

(Here the values are as follows: Effect size = 0.25, Alpha error = 0.05, power = 0.8, Number of groups = 2, Number of measures = 3.)

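### The Phase 1 survey excludes workshop attendees and anyone with any illness, so it describes a narrower group than the tribal population named in its objective

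*Protocol article*

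**What the plan says.** The first objective, under Aims and Objectives, is to "Determine the awareness, attitude and mental help seeking intention regarding common mental health problems among the tribal population using standardized tools". The Abstract describes Phase 1 in the same terms: "a house-to-house survey will be conducted among the selected colonies of Koraga tribe to determine their awareness, attitude, and mental help seeking intention". The Sample size section plans the survey around the proportion of the tribe that is aware, set at 0.5, with a precision of 0.05.

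The Eligibility criteria section first gives the Phase 1 inclusion rule: "People aged between 18-60 years will be selected in a stratified manner (age and gender"). It then gives a single exclusion list: "exclusion criteria for both Phase 1 & 2 will be those individuals who have attended previous mental health workshops", together with "those who have any acute/chronic illness". The list names both phases. The article gives no reason for applying it to the survey, sets no limit on the type or severity of illness, and does not say how many people it is expected to remove. The Limitations section does not mention it.

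**The concern.** Phase 1 is a descriptive survey, so the people who may be sampled should match the people the result is about. Here they do not. The objective and the planning proportion concern the tribe; the eligibility rule admits only those without illness and without earlier workshop exposure.

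The first exclusion bears directly on the outcome. Someone who has attended a mental health workshop is likely to know more about mental health, so removing such people selects on a cause of awareness. That is sensible in Phase 2, where the training should be tested in people who have not been trained before, but a population survey has no comparable need for it. The illness exclusion is very broad as worded, and illness could plausibly be related to attitudes and to the intention to seek help.

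Two things are at stake. Objective 1 would be reported for a population that was not surveyed. In addition, the Intervention section says that the knowledge gaps found in the survey go into the training module, so a gap measured in a restricted group would shape what is taught.

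**Working it through.** **Step 1. The plan's own figure.** Inputs from the Sample size section: 95% confidence, P = 0.5, d = 0.05.

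n = Z² P(1 - P) / d² = 1.96² × 0.5 × 0.5 / 0.05² = 3.8416 × 0.25 / 0.0025 = 384.16

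This reproduces the stated 384, rounded to 400. (The sentence beginning "In this formula the confidence level is 95%, hence Z" prints 1.96 as the value of Z². Taken literally that would give 196, so it is a misprint and the result is right.) At n = 400 the standard error is √(0.25 / 400) = 0.025 and the half-width is 1.96 × 0.025 = 0.049, or 4.9 points. The formula has no term for eligibility, so n stays the same whether or not the exclusions are kept.

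**Step 2. The bias.** Let e be the share of the target population that is excluded, and let D be awareness among the eligible minus awareness among the excluded. Population awareness is (1 - e) × P_eligible + e × P_excluded. The survey estimates P_eligible, so

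bias = P_eligible - P_population = e × (P_eligible - P_excluded) = e × D

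Sample size does not enter.

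**Step 3. Range.** The document gives neither e nor D. Both are assumptions here, with D between 10 and 30 points in absolute size.

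| Excluded share e (assumed) | Bias at D = 10 points | Bias at D = 30 points | D at which the bias equals 5 points |
|---|---|---|---|
| 5% | 0.5 points | 1.5 points | 100 points |
| 10% | 1 point | 3 points | 50 points |
| 20% | 2 points | 6 points | 25 points |

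**Step 4. Effect on the confidence interval.** With bias b and SE = 0.025, actual coverage of a nominal 95% interval at n = 400 is Φ(1.96 - b/SE) - Φ(-1.96 - b/SE), under a normal approximation and simple random sampling. Coverage is about 93% at a bias of 1 point, 87% at 2, 78% at 3 and 33% at 6.

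**Step 5. Direction.** For workshop attendees D is likely to be negative, because they should be more aware than the rest, so awareness would be understated. For ill people the document offers nothing that fixes the sign. The two effects could add up or partly cancel.

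**Step 6. Is the illness exclusion likely to be trivial?** The Background reports liver dysfunction from chronic alcoholism in this tribe, and describes drinking as widespread: "as evident by majority (75%) of them being alcoholics". An exclusion for any chronic illness, read literally, could therefore remove a material share. How large a share is not stated.

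**The case against.** The strongest reply is about size. The document does not say how many people either rule removes. It describes poor access to primary health care and little effort so far to improve mental health among tribal people, so workshop attendance may be rare. If only 2% were excluded and the difference were 30 points, the bias would be 0.02 × 30 = 0.6 points, which is negligible against a precision of 5. This stands: the bias may be small, and that is why a range is shown.

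A reader might infer from the 75% alcoholism figure that up to three quarters of adults would be turned away. The document does not support that. The figure comes from a cited study, nothing says that alcoholism counts as illness for eligibility, and a fuller protocol may define the term. The figure shows only that a literal reading may not be harmless.

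It can also be said that the survey serves to design training for people who have had none, so measuring the gap in workshop-naive adults suits that use. This has some force for the module, but it does not fit Objective 1, which is stated without that restriction.

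Further, the tools yield scores (a 25-item knowledge questionnaire, a 40-item attitude scale, a 1-7 intention mean), and the proportion aware appears only as a planning value. The percentage-point figures above therefore illustrate awareness alone and do not measure the effect on attitude or help-seeking intention.

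Finally, the three blocks are chosen by convenience, which limits generalisation to the tribe even without these exclusions. That is true, and it is a separate limit. It does not justify adding another one.

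**Conclusion.** The mismatch holds: the eligibility rule for Phase 1 defines a narrower population than the objective and the sample-size parameter, and the article neither justifies nor acknowledges it. The result would apply to adults aged 18-60 free of illness and workshop exposure.

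A reader might go further and infer that Phase 1 cannot estimate its target at all, or that awareness will certainly come out too low. Neither follows. What can be said is that the estimate carries a bias of unknown size. It points towards understatement for the workshop exclusion and has no known direction for the illness exclusion, so the net direction is open. Under the assumed inputs the bias runs from 0.5 points (5% excluded, 10-point difference) to 6 points (20% excluded, 30-point difference), that is, from negligible to more than the planned precision. This is worth correcting, mainly because the correction is simple and data collection had not begun.

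**What to change.** For Phase 1, drop both exclusions and keep only inability to consent or to respond. Record earlier workshop attendance and current illness on the background form, if its 15 items do not already cover them (the form is not shown), and report the survey results by these two items as well as overall.

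If the exclusions are kept, restate the Phase 1 target population to match them in the objective and the sample-size text, and report the number of people excluded for each reason.

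Keep the workshop exclusion for Phase 2.

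The cost is an edit to the eligibility paragraph, at most two form items and, since ethics approval and trial registration are already in place, probably an amendment to each. The sample size does not change. The Study status section says that data collection had not started and the pilot of the survey was still being planned. The convenience choice of blocks will remain as a separate limit on generalisation and should be reported as such.

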### Data collection

For Phase 1 data will be collected using standardised tools like Mental Health Knowledge Questionnaire (MHKQ), Community Attitude towards Mentally Ill scale (CAMIS), and Mental Help Seeking Intention scale (MHSIS). Administrative permissions for the data collection is obtained. The data will be collected from the participants after explaining the participant information sheet and obtaining informed consent. Data collection will be carried over six months due to geographical constraints.

For Phase 2, identification of the participants for the GTP i.e the leaders/representatives of the selected tribal colonies will be done with the help of Department of Tribal Welfare, at the district administrative office. The project staff will approach the selected leaders/representatives of the tribal colonies, explain the participant information sheet, obtain consent and then proceed with data collection. Data for pre-test and multiple post-test (at 0, 6, 12 months) will be collected using standarised tools such as MHKQ, CAMIS, MHSIS and Gatekeeper Behavior Scale (GBS). The project staff will be present during the data collection procedure in both phases of the study.

Confidentiality of the data collected: The consent forms will be coded, and any identification data will be concealed thoroughly for both phase 1 and phase 2. The data collection for phase 1 will be done through house-to-house survey using structured questionnaires and data collection for phase 2 of the study will be done during the GTP, that is, the two-day workshop. Structured questionnaires will be used to collect the data. There is no in-depth interviews or verbatim reports involved in this study, however if the participants need any clarifications while filling out the structured tools, the primary investigator will be there to clarify it.

### Data collection instruments

Permission from the authors of the following standardised tools (except socio-demographic) are obtained.

Tool 1: Background information consists of 15 items related to the socio-demographic characteristics of the participants. This tool is developed by the researcher and subjected to validation by experts.

Tool 2: The Mental Health Knowledge Questionnaire is a dichotonoums scale consisting of 25 items regarding substance use disorder, depression, suicide, stress, anxiety, its treatment and prevention. Higher the scores attained on this scale indicates greater mental health literacy. This scale was developed by Hanhui Chen, Zhizhong Wang and Michael Roberts in 2013.

Tool 3: The Community Attitude towards Mentally Ill scale is 40 item Likert scale measuring the attitude towards mental illness and mentally ill people under four dimensions namely authoritarianism, benevolence, social restrictiveness, and community mental health ideology. Higher the score on CAMIS, indicates greater stigma toward mental illness and a mentally ill person. This scale was developed in 1970’s by Martin Taylor and Michael Dear, Canada.

Tool 4: Mental Help Seeking Intention scale (MHSIS) is a 3-item instrument designed to measure respondents’ intention to seek help from a mental health professional if they had a mental health concern with responses ranging from strongly agree (7) to strongly disagree (1). The resulting mean score will range from a minimum of 1 to a maximum of 7. A higher score indicates a greater intention to seek help. This scale is an adapted version from Ajzen’s Theory of Planned Behaviour (2006) and was standardised by [name] H Hammer and Douglas Spiker in 2018.

Tool 5: Gatekeeper Behavior Scale is a Likert scale consisting of 11 items evaluating the preparedness (5 items), likelihood (2 items), and self-efficacy (4 items) of an individual’s gatekeeping skills. Higher scores indicate better gatekeeping skills of the individual. This scale was developed by Albright, G., Davidson, J., Goldman, R., Shockley, K. & Mitchell-Timmons, J. in 2014.

### Intervention

Gatekepeer Training Program (GTP) is a two-day mental health workshop.

The content for the workshop (module) is being prepared by the primary investigator. Knowledge gap observed from phase 1 (survey) of the study is included in the module. This module will be given to a panel of experts in various fields of psychiatry at local, national, and international level. The suggestions and modifications will be incorporated accordingly.

The program will be implemented by the same multi-disciplinary team members in various community locations as per the convenience of the participants or at a single location if all participants (54) could meet up conveniently.

The investigator will be in contact with the participants throughout the post-intervention period to review/clarify the issues faced by the gatekeepers, and a diary will be provided to the participants in which they will have to document the details of interactions (if they had) with people having mental health concerns. (The sessions for the two-days workshop is listed in
Table 1.) The control group in the study will receive a module on the theoretical concepts of common mental health problems and gatekeeper behaviour. For both the experimental and control group, post-test will be conducted at three points of time i.e., at 0, 6, 12 months. After the follow-up duration of one year, a half-day workshop will be conducted for the control group at various community locations (as per the convenience of the participants). This workshop will focus on the theoretical concepts of the module provided earlier.

**Table 1. T1:** Outline of the two-day workshop on GTP.

Sl	Topic	Time	Resource person
**Day 1**			
1	Introduction to Concepts of Mental Health	9:00-10:00am	Principal investigator (Psychiatry nurse)
2	Types of common mental health problems	10:30-12:30am	Principal investigator
3	Early identification and treatment	2:00-3:00pm	Consultant Psychiatrist
4	Strategies in prevention	3:00-4:00pm	Psy. Social Worker
5	Tribal health and welfare	4:00-5:00pm	Representative Dept. of Tribal Welfare Udupi District
**Day 2**			
6	Introduction to QPR (Question, Persuade, Refer) technique	9:00-1:00pm	Principal investigator
7	Importance of Counselling with role plays, case discussion and paired learning	2:00-4:30pm	Consultant Psychiatrist Psy. Social Worker
8	Conclusion	4:30-5:00pm	Principal investigator

Table 1 depicts the sessions along with the resource person that will be included in the two-day GTP workshop during the Phase 2 of the study.

**Validity and reliability:** All the tools (except socio-demographic proforma) that will be used in this study are standardised tools and are validated internationally. Since the study population is local tribal population, the tools are translated into the language known by the tribals (Kannada). Re-translation back to English is done by language experts. Since the primary investigator is fluent and well versed in the local language (Kannada), extensive training was not required for the application of tools in local languages.

Both the English and Kannada versions were subjected to cross cultural validity through experts in the field of psychiatry, psychiatric nursing, psychiatry social workers, and clinical psychologist. These experts have extensive experience in working with the people of Koraga tribe.

The experts agreed that the tools could be used in a tribal population.

Inter-rater and intra-rater reliability is not applicable to this study as only the primary investigator will be recording the data throughout the study period and this study involves only a single trial with follow ups. However, the tools used in this study were tested for reliability and the values are mentioned below: (refer
Table 2)

**Table 2. T2:** Reliability testing of the study tools.

Tool	Test done	Reliability
MHKQ (Yes/No)	Kuder-Richardson	0.97
CAMIS (Likert scale)	Cronbach alpha	0.75
MHSIS (Likert scale)	Cronbach alpha	0.89
GBS (Likert scale)	Cronbach alpha	0.79

Table 2 shows the reliability values for the data collection tools of the study.

**Ethical consideration:** Permission to conduct the study is received from the Head of the Institution, Institution Review Committee and Institutional Ethics Committee (322/2020). Permission is also obtained from the tribal community authority (Integrated Tribal Development Office) at the district government office of Udupi. This study is registered in Clinical Trial Registry of India (CTRI/2021/06/034037 [Registered on: 07/06/2021]. Informed consent will be obtained from all participants, and a complete explanation of the investigation will be provided.

Participation in this study is voluntary; the participants may decline to participate at any time, and they need not give any reason for the same, and such withdrawal shall be without penalty. If they withdraw from the study before data collection is completed, the data collected until they indicated withdrawal will be used in the study report. The sample size is calculated by keeping in mind the attrition rate at 20%, hence the sample size will not be affected with the drop-outs.

**Data analysis:** Demographic characteristics of the study participants will be presented in descriptive summary tables. The outcome variables across the follow up period will be analyzed by repeated measures of ANOVA. The categorical variables will undergo bivariate analysis by applying the Chi-square test for categorical variables. A p-value of less than 0.05 will be considered the criteria for statistical significance. Overall SPSS 26 version will be used to analyse the data gathered.

**Dissemination of results:** The results will be disseminated via presentations at appropriate scientific conferences and workshops. The findings will also be published in peer-reviewed journals, professional and institutional repositories etc. The result will be discussed with the Department of Tribal Welfare and other stakeholders for improvement of mental health awareness, accessibility to meantal health care and appropriate utilization of community-based resources.

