## Methods

### Research approach and design

The study is based on an evaluative approach to meet its objectives. The study will be done in two phases. Phase 1 will be a cross-sectional house-to-house survey where data will be collected from the Koraga tribe and Phase 2 will have a quasi-experimental design which includes an experimental and a control group. There will be pre-test and post-test for both the groups with multiple follow ups at 0, 6 and 12 months. GTP (intervention) will be carried out only for the experimental group.

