### Sampling technique

Phase 1: Based on convenient sampling technique, out of the seven blocks, three blocks will be taken up for the survey. Each of these three blocks comprises a minimum of 35 colonies, hence 25-27 colonies will be selected randomly from each block. Stratified sampling technique (age and gender) will be used to select five samples/colony for the survey.

For phase 2, convenient sampling technique will be used to select the block (largest block) for experimental and control group. These largest blocks consist of 85-90 colonies, hence 55 colonies will be selected randomly. Further purposive sampling technique will be used to select the participants for GTP (
Figure 1: Schematic representation of sampling technique).

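### Phase 2 is not randomised, yet the stated analysis is a repeated measures ANOVA with no covariates, so an arm difference in characteristics that affect learning would be counted as GTP effect

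*Protocol article*

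**What the plan says.** All references are to the protocol article.

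- Research approach and design: "Phase 2 will have a quasi-experimental design which includes an experimental and a control group". No random allocation is described.
- Sampling technique: "convenient sampling technique will be used to select the block (largest block) for experimental and control group". Colonies are then drawn at random: "These largest blocks consist of 85-90 colonies, hence 55 colonies will be selected randomly". The people are not: "Further purposive sampling technique will be used to select the participants for GTP".
- Eligibility criteria: both block leaders and colony representatives may enter. Both arms share the same criteria, including literacy in Kannada and no earlier mental health workshop.
- Data collection instruments, Tool 1: "Background information consists of 15 items related to the socio-demographic characteristics of the participants". The items are not listed.
- Data analysis: "Demographic characteristics of the study participants will be presented in descriptive summary tables". For the outcomes: "The outcome variables across the follow up period will be analyzed by repeated measures of ANOVA". There is one further test: "The categorical variables will undergo bivariate analysis by applying the Chi-square test for categorical variables".

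No covariate, matching or other control of confounding is named anywhere, and the Limitations section does not mention non-random allocation.

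**The concern.** In a randomised trial, an unadjusted comparison is unbiased because allocation balances the arms on average. Here nothing in the allocation does that. Drawing colonies at random within a block makes them represent the block; it does not allocate them to an arm.

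An arm with more schooling, a different age mix or more block leaders could plausibly gain more from a workshop, or from the written module that the control group receives. The named analysis has no term for this, so the difference would appear in the group effect and its p-value. It could run either way: inflate the GTP effect if the experimental arm learns more readily, or mask it if the control arm does. A descriptive table, or a chi-square test between arms, would show an imbalance but would not correct the estimate. The third study objective is the effectiveness of the GTP, so this comparison carries the main conclusion.

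**Working it through.** **Step 1. Which test the sample size fits.** Sample size section: effect size f = 0.25, alpha 0.05, power 0.8, 2 groups, 3 measures, N = 86, then 108 with 20% attrition. The correlation between measures is not stated; I assume 0.5.

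- Between-group test: λ = f²·N·m / (1 + (m − 1)ρ) = 0.0625 × 86 × 3 / 2 = 8.06 on 1 and 84 df, power 0.801. N = 84 gives 0.792, so 86 reproduces exactly, and 86 / 0.8 = 107.5, rounded up to 108.
- Group-by-time test: λ = f²·N·m / (1 − ρ) reaches 80% power at N = 28. With ρ of 0.3 or 0.7 it needs 38 or 18. None is near 86.

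The stated size therefore fits a between-group main effect. Unlike group-by-time, that test does not even remove level differences present before training.

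**Step 2. Bias.** All inputs here are assumed. Suppose a fraction p of one arm and 1 − p of the other is better educated, these people gain g SD more at every post-test, the pre-test is level between arms, and the GTP has no effect. The spurious group difference is g(2p − 1):

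- g = 0.5, 65/35: 0.5 × 0.30 = 0.15 SD. With two equal groups f = 0.25 equals 0.5 SD, so this is 30% of the planned effect.
- g = 0.5, 60/40: 0.10 SD.
- g = 0.3, 60/40: 0.06 SD.

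**Step 3. False-positive rate, 43 per arm, ρ = 0.5.** The outcome is the mean of the three post-tests.

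- Variance with group only: (1 + 2ρ)/3 = 0.667.
- With the pre-test as covariate: 0.667 − ρ² = 0.417.
- As change from pre-test: 0.667 + 1 − 2ρ = 0.667.
- Each gains g²p(1 − p) from education, and SE = √(2V/43).

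For g = 0.5 and 65/35 the added term is 0.25 × 0.65 × 0.35 = 0.057:

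- Group only, or change score: V = 0.724, SE = 0.183, bias/SE = 0.82, rejection about 12.8%.
- Pre-test as covariate: V = 0.474, SE = 0.148, bias/SE = 1.01, rejection about 17.0%.

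Rejection rates from the noncentral t, with simulated values (4,000 runs per setting) in brackets; the last column is simulated only:

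| Gain difference, split | Group only | Pre-test as covariate | Pre-test and education |
|---|---|---|---|
| 0.5 SD, 65/35 | 12.8% (12.9%) | 17.0% (17.1%) | 6.0% |
| 0.5 SD, 60/40 | 8.4% (8.9%) | 10.2% (11.1%) | 5.6% |
| 0.3 SD, 60/40 | 6.3% (6.8%) | 7.0% (7.3%) | 5.1% |

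Using the pre-test alone does not help under this mechanism. The bias is unchanged and the standard error is smaller, so the false-positive rate rises. Adding education brings the simulated bias to about zero.

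**Step 4. When the pre-test is enough.** If education raises pre-test and post-test scores equally (0.5 SD, 65/35), the difference in change has bias of about 0.00 SD and a simulated rejection rate of 5.3% without any covariate. The problem is differential gain, not level.

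**The case against.** The strongest objection is that this reads too much into a short paragraph of a condensed article. Repeated measures ANOVA can carry covariates, model terms are not listed, and a covariate list often sits in a fuller plan. This stands in part: the article does not rule adjustment out. It does, however, fix the test, the significance level and the software for a comparison that allocation does not protect, and the sample size fits a plain between-group test. Carried out as written, the analysis controls no confounder.

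Three further points stand and limit the claim.

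- A reader might infer that the background items serve description alone. The chi-square sentence may cover categorical demographics, so that is not established. What holds is that they have no adjusting role.
- A reader might infer that the arms do differ and that the result will be biased. No part of the article shows an imbalance. Shared eligibility criteria, one tribe, one district and random colonies within blocks all limit it.
- The size rests on assumed inputs and one mechanism, differential gain. Where education only shifts level, group-by-time copes (Step 4). But the article does not say that group-by-time is the test to be used.

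It is also true that adjustment for individual characteristics cannot separate the GTP from differences between the blocks themselves.

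**Conclusion.** The point holds in conditional form. The stated analysis leaves any arm difference in characteristics that affect learning inside the GTP estimate, and the pre-test protects only against stable differences in level. With 43 per arm, correlation 0.5 and a null effect, the false-positive rate is about 6-7% in the mildest case examined and about 13-17% in the strongest, against about 5-6% with adjustment; the bias is 0.06 to 0.15 SD. These figures illustrate what could happen and do not predict this trial's result. The imbalance and the gain differences are assumptions, and it is also assumed that Tool 1 records education and role. The harm is small at the mild end. The change is still worth making because it costs little and, by the Study status section, data collection had not begun. Covariates chosen after the results are seen would be open to selective adjustment.

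**What to change.** In the Data analysis paragraph, make the reported Phase 2 group comparison a model adjusted for the pre-test score and a short, prespecified set of covariates from Tool 1: age, gender, education and role (block leader or colony representative), so far as the form records them. Apply it to all four scales and keep the unadjusted ANOVA as a sensitivity analysis. State that adjustment covers measured differences only and does not remove differences between the blocks.

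The cost is a sentence or two, and no new data if the form holds these items. The pre-test and four covariates at one degree of freedom each take the residual from 84 to 79. Precision need not suffer: in simulated balanced arms with a true 0.5 SD effect, power was 76% with group alone, 90% with the pre-test and 93% with the pre-test and education.
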